## Abstract

**Background:**

COVID-19 is a recent major public health concern caused by the SARS-CoV-2 virus, with approximately 44.6 million COVID-19–positive cases and 530,000 deaths in India (as of February 1, 2023). The COVID-19 vaccination drive in India was initiated in January 2021; however, an effective preventive strategy with high efficacy and immunological safety remains elusive.

**Objective:**

The aim of this study is to assess the immunogenic responses of *Arsenicum album* 30CH (AA30CH) as COVID-19 prophylaxis, including assessment of immunological markers, innate and acquired immune responses, COVID-19 symptoms, and its associated antibody responses.

**Methods:**

This randomized controlled clinical trial (RCT) will include two parallel comparator groups of AA30CH and placebo with an allocation ratio of 1:1 conducted in the Pathanamthitta district of Kerala, India. The placebo or AA30CH will be administered in three intervention schedules and blood samples will be collected before and after each of the intervention schedules. Based on the inclusion and exclusion criteria, 112 participants per arm (with an expected dropout of 20%) will be screened. Immunogenic responses will be evaluated by determining the antigen density and modulation in immunological markers and lymphocyte subsets CD3, CD4, CD8, CD24, CD27, CD38, CD4 interferon-γ, CD4 CD17, CD4 CD25 (activated T lymphocytes), T cells, B cells, dendritic cells (mature and immature), and natural killer cells on days 1, 5, 23,27, 45, 49, and 66. The innate and acquired immune responses will also be evaluated by a real-time reverse-transcriptase polymerase chain reaction (RT-PCR) array profiler (84-gene set) before and after the study interventions. The toxicity status of AA30CH in study participants will be evaluated through hepatic, renal, and hematological parameters and peripheral smears on days 1, 5, 23, 27, 45, 49, and 66. The number of participants developing COVID-19–like symptoms per National Centre for Disease Control guidelines and the number of participants testing positive for COVID-19 in RT-PCR during follow-ups in any of the three intervention schedules will be identified. Moreover, a subgroup analysis will be used to assess the COVID-19 antibody responses between vaccinated and unvaccinated participants.

**Results:**

This RCT protocol has been approved by various committees and funded by the Central Council for Research in Homoeopathy, Ministry of Ayush, Government of India. The project has been implemented in collaboration with the Department of Homoeopathy, Government of Kerala. The RCT was rolled out on January 25, 2023, and enrollment was completed April 3, 2023. The immunological assays will be conducted at the Department of Biotechnology-Translational Health Science and Technology Institute, Faridabad, India.

**Conclusions:**

This study will represent the first evaluation of the immunological efficacy and safety of AA30CH in an RCT, which may significantly impact the use of homeopathy as an evidence-based medicine approach.

**Trial Registration:**

Clinical Trials Registry-India CTRI/2022/08/045089; https://tinyurl.com/mryrpkvk

**International Registered Report Identifier (IRRID):**

DERR1-10.2196/48479

## Introduction

COVID-19 infection caused by SARS-CoV-2 is a recent major public health burden leading to clusters of mild to moderate respiratory illnesses. COVID-19 became a pandemic affecting more than 200 countries worldwide owing to its high infectivity [1,2]. COVID-19 infection is accompanied by an aggressive inflammatory response that releases several proinflammatory cytokines [3,4]. The host immune response to the SARS-CoV-2 virus is hyperactive, resulting in an excessive inflammatory reaction [5]. The incubation period of COVID-19 was reported to be 2-14 days [6,7]. It is currently believed that SARS-CoV-2 is most likely of zoonotic origin [8-10] and transmits from person to person by infected droplets, with more severe infections mainly found in older people and those suffering from comorbidities [11,12].

The World Health Organization (WHO) dashboard of COVID-19 reported approximately 753,479,439 confirmed cases of COVID-19, including 6,812,798 confirmed deaths (as of January 31, 2023) globally. The United States has been declared the country with the highest number of cases, followed by China, India, France, Germany, Brazil, Japan, the Republic of Korea, Italy, the United Kingdom, the Russian Federation, Turkey, and Spain, respectively (as of January 31, 2023) [13]. As per official reports of the Government of India, the country reported 44,682,895 COVID-19–positive cases with 530,740 deaths as of February 1, 2023. The Indian states of Maharashtra and Kerala reported the highest number of cases. Maximum deaths were reported in the second wave of COVID-19, which peaked in May 2021 [14]. The Government of India initiated the COVID-19 vaccination drive in January 2021. Nevertheless, an effective preventive measure needs to be identified with evidence of breakthrough infections and reduced protection against the Delta variant of SARS-CoV-2.

Several therapeutic strategies and clinical evaluations are ongoing to combat SARS-CoV-2 infection; however, no effective treatment has been developed with immunological safety. The WHO initiated a large global, randomized clinical study on four therapies (remdesivir, hydroxychloroquine, lopinavir/ritonavir, and interferon [IFN] therapy), showing that all four therapies had little or no influence on overall mortality, ventilation initiation, or hospital stay for hospitalized patients [15]. Furthermore, the usage of antibiotics in patients with COVID-19 raises the risk of harmful consequences such as antibiotic resistance [16,17].

Homeopathy has been vital in preventing epidemics, especially before modern sanitation, antibiotics, and vaccinations [18]. Homeopathy has also displayed effectiveness in combating many outbreaks in its history of 200 years, such as scarlet fever in 1799 [19], leptospirosis in 2007 [20], and dengue fever in 2018 [21,22]. Homeopathy has also been successfully documented in the medical literature for both the treatment and prophylactic use of flu-like epidemics such as the “Spanish” flu of 1918 [23], “Asian” flu of 1951 [24], and H_1_N_1_ influenza pandemic of 2009-2010 [25]. The homeopathic formulation *Arsenicum album* 30CH (AA30CH) was previously reported to be effective in various respiratory diseases such as swine flu, influenza-like illness, and other respiratory illnesses [25-29]. In one study, *Arsenicum album*, as one of the constituents of 7X-24X complex, exhibited nuclear factor-κB hyperactivity according to reduced expression of the reporter gene in green fluorescent protein-transfected HT29 cells and also reduced the release of tumor necrosis factor-α in macrophages [30]. Due to the looming threat of the COVID-19 pandemic and the lack of effective treatments, alternative preventive strategies need to be established.

During the pandemic, AA30CH was advised as a preventative medicine for COVID-19 by the Ministry of Ayush, Government of India, toward the end of January 2020 [31]. A subsequent advisory issued by the Ministry of Ayush on March 6, 2020, also mentions the immunomodulatory action of AA30CH [32]. However, the exact role of AA30CH in innate immunity against COVID-19 was not fully understood. The observation that individuals with underlying diseases are more susceptible to severe illness than healthy people or young children is mainly attributed to the low efficacy of the innate immune response [33]. Therefore, the aim of this study is to investigate the cellular pathways related to innate and adaptive responses to AA30CH using flow cytometry–based immunological assays and gene expression analysis of 84 vital genes with a real-time reverse transcription-polymerase chain reaction (RT-PCR) array profiler. This PCR array profiler includes genes related to the interleukin-1 receptor (IL-1R) and Toll-like receptor (TLR) signaling pathways, including IL-1R and TLR genes involved in the sensing of pathogens. Genes related to host defense are also represented in this array, including the acute-phase response, complement activation, the inflammatory response, and the antiviral humoral response.

Moreover, gene expression profiling of human natural killer (NK) cell responses will also be investigated. This randomized controlled clinical trial (RCT) is being conducted by the Central Council for Research in Homoeopathy (CCRH), an apex research body under the Ministry of Ayush, Government of India, in the Pathanamthitta district of Kerala state, in close collaboration with the District Medical Office (under the Department of Homoeopathy, Government of Kerala) after signing an agreement with the Government of Kerala. The CCRH also signed a Memorandum of Understanding with the Department of Biotechnology-Translational Health Science and Technology Institute (DBT-THSTI), Faridabad, a Coalition for Epidemic Preparedness Initiative–approved laboratory facility under the Government of India for conducting the immunological assays as part of the primary objective of the study.

The primary objectives of the study are to elucidate the immunogenic responses of AA30CH in COVID-19 prophylaxis by determining the antigen density and identifying the variation in immunological markers and lymphocyte subsets CD3, CD4, CD8, CD24, CD27, CD-38, CD4 IFN-γ, CD4 CD17, CD4 CD25 (activated T lymphocytes), T cells, B cells, dendritic cells (DCs; mature and immature), and NK cells; and to estimate the innate and acquired immune responses by real-time RT-PCR array analysis (see Multimedia Appendix 1). The secondary objectives of the study are the toxicological evaluation in study participants who took either a placebo or AA30CH, limited to hepatic, renal, and hematological parameters, by conducting liver function tests (LFTs), renal function tests (RFTs), complete blood count (CBC), and peripheral smear; to identify the number of participants developing COVID-19–like symptoms as per National Centre for Disease Control (NCDC) guidelines during follow-ups in any of the three intervention schedules; to identify the number of participants testing positive for COVID-19 in RT-PCR during follow-ups in any of the three intervention schedules; and to determine the COVID-19 antibody responses between vaccinated and unvaccinated participants.

## Methods

### Study Design

This clinical trial is designed as a randomized, double-blind, placebo-controlled clinical study with two parallel comparator arms of AA30CH and placebo, using an allocation ratio of 1:1. The participants will be enrolled and randomized only after two phases of initial screening (screenings I and II), followed by three schedules of intervention and follow-ups in the intervention phase of 66 days. The flow chart of the study design is represented in Figure 1. The protocol is reported following the SPIRIT (Standard Protocol Items: Recommendations for Interventional Trials) 2013 guidelines.

**Figure 1 figure1:**
[figure not shown]
Flow diagram of the screening and randomization of the participants. D: day; DC: dendritic cell; IFN: interferon; IL: interleukin; NK: natural killer; NHRIMH: National Homoeopathy Research Institute in Mental Health; RT-PCR: reverse transcription-polymerase chain reaction; TNF: tumor necrosis factor; V: visit.

### Study Setting

This RCT will be implemented in the 10 government homeopathic dispensaries/hospitals located in 10 different panchayats of the state of Kerala in India, identified by the District Medical Officer (Pathanamthitta District), Department of Homoeopathy, Government of Kerala, based on the higher incidence of COVID-19 and elevated test positivity rate (TPR). These identified study sites are: (1) Government Homoeopathic Dispensary, Elanthoor panchayat; (2) Government Homoeopathic Dispensary, Naranganam panchayat; (3) Government Homoeopathic Dispensary, Kulanada panchayat; (4) Government Homoeopathic Dispensary, Pandalam panchayat; (5) Government Homoeopathic Dispensary, Ezhamkulam panchayat; (6) Government Homoeopathic Dispensary, Puthusserimala Ranni panchayat; (7) Government Homoeopathic Dispensary, Mezhuveli panchayat; (8) Ayush Primary Health Centre Homoeopathy (under National Health Mission, Government of India), Ranni Angadi panchayat; (9) Government Homoeopathic Dispensary, Ayush Health and Wellness Center, Kuttappuzha panchayat; and (10) Government Homoeopathic Hospital, Kottanad panchayat. The National Homoeopathy Research Institute in Mental Health (NHRIMH), located in the Kottayam district of Kerala state under the CCRH, Government of India, is designated as the facilitating institute of the study with prior approvals, and two nodal site principal investigators (PIs) and supporting team will operate from the NHRIMH during the RCT. The PI will form monitoring teams who will visit the 10 study sites on all blood draws and on intervention days of the trial and report to the competent authorities in real time.

### Eligibility Criteria

#### Inclusion Criteria

Apparently healthy male and female participants, aged 18-60 years, residents of the Pathanamthitta district of Kerala, with negative COVID-19 RT-PCR test reports at least 48 hours before the first day of the intervention, and those who have not taken *Arsenicum album* medicine in any homeopathic potencies in the past 4 months will be included in the study; both COVID-19 vaccinated and unvaccinated participants will be eligible for inclusion.

#### Exclusion Criteria

Participants with a positive COVID-19 RT-PCR test report at least 48 hours before the first day of the intervention; those with history of severe viral diseases in the past 3 months, such as herpes zoster, dengue, chikungunya, and chicken pox; those having a history of chronic respiratory ailments with shortness of breath as a recurring symptom; and those taking concomitant medications such as immunosuppressants, hormonal therapies, or Ayush therapies for chronic ailments will be excluded from the study.

### Sample Size

The study is aimed at evaluating the immunologic responses of AA30CH. The study is based on earlier encouraging leads provided through community studies on the role of AA30CH in preventing COVID-19. Several parameters are in consideration for the evaluation of immunogenic responses. With regard to the computation of sample size, based on the literature and expert opinions, it is proposed to consider some limited immunologic parameters that are more relevant. Owing to the scarce availability of literature, it would be quite challenging to hypothesize the assumption. Assuming a type 1 error of 5% and a power of 80%, it was estimated that there would be 93 participants each in the intervention and control groups, with a total of 186 participants. This could be escalated based on attrition due to loss in follow-up. If this loss to follow-up is considered at 20%, a total of 112 participants have to be enrolled in each group, with a total sample of 224 that would need to be recruited for the study.

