### Outcome Measures

The primary outcome measures of the study are the estimation of antigen density and modulation in immunological markers (CD3, CD4, CD8, CD24, CD27, CD38, CD4 IFN-γ, CD4 CD17, CD4 CD25 [activated T lymphocytes], T cells, B cells, DCs [mature and immature], and NK cells) observed from the blood sample drawn 1 day before and after 3 days of the intervention (ie, on days 1, 5, 23,27, 45, and 49) and at the end of the study (day 66), along with the innate and acquired immune responses from the blood sample drawn on days 1, 23, 45, and 66 of the study interventions.

The secondary outcome measures of the study are to evaluate the toxicity status of study participants who have taken AA30CH or placebo based on hepatic, renal, and hematological parameters and peripheral smears 1 day before and after 3 days of the intervention (ie, on days 1, 5, 23, 27, 45, and 49) and at the end of the study (day 66); the number of participants developing COVID-19–like symptoms as per NCDC guidelines during follow-ups in any of the three intervention schedules; and the number of participants with COVID-19–like symptoms who test positive for RT-PCR during follow-ups in any of the three intervention schedules.

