### Statistical Analysis

Data analysis will be performed following the intention-to-treat/per-protocol method. The safety and immunological parameters will be analyzed at each of the seven time points and comparisons will be made between the subjects and groups. Additional analyses (eg, subgroup analyses according to age, sex, and perceived risk categories) will also be performed based on the evolving trends from the analysis. A trial statistician will be engaged for the statistical analysis of the clinical trial.

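### The stated 5% type I error and 80% power are not shown to hold together for the large primary set that the article declares

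*Protocol article*

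**What the plan says.** **Sample Size (Protocol article, Methods).** Because many parameters are of interest, "it is proposed to consider some limited immunologic parameters that are more relevant". None is named. The section concedes that "Owing to the scarce availability of literature, it would be quite challenging to hypothesize the assumption", and it gives no effect size, standard deviation, test or time point. It then states one error rate, one power and one number per arm: "Assuming a type 1 error of 5% and a power of 80%, it was estimated that there would be 93 participants each", which makes 186 in total. For attrition it adds: "If this loss to follow-up is considered at 20%, a total of 112 participants have to be enrolled in each group".

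**Outcome Measures.** "The primary outcome measures of the study are the estimation of antigen density and modulation in immunological markers". The list that follows is CD3, CD4, CD8, CD24, CD27, CD38, CD4 IFN-γ, CD4 CD17, CD4 CD25, T cells, B cells, mature and immature dendritic cells, and NK cells, on days 1, 5, 23, 27, 45, 49 and 66. The innate and acquired immune responses on days 1, 23, 45 and 66 are primary as well. The Abstract and the Introduction show that these responses are measured with an 84-gene RT-PCR array. The primary objectives at the end of the Introduction cover the same ground.

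**Statistical Analysis.** "The safety and immunological parameters will be analyzed at each of the seven time points and comparisons will be made between the subjects and groups". No marker, gene or visit is singled out, and no hierarchy, composite or division of alpha is given.

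**The concern.** The sample size speaks of a limited set and carries a single alpha and a single power. The outcome section declares a very large primary set, and the analysis section compares groups visit by visit. If all of these are followed as written, the article does not say which comparison decides the trial, and any of a large number of results could be reported as its primary finding.

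What is at stake is the claim of immunological efficacy, which the Discussion calls the trial's main emphasis. If each primary comparison is tested at 5%, the chance of at least one false positive is well above 5%. If the primary family is protected at 5%, a given effect on a single marker is detected less often than in one unadjusted test at the same sample size.

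The choice of primary outcomes, and the endpoint behind the sample size, are fixed in the article itself. An unseen analysis plan could add an adjustment, but it would not reconcile those two statements.

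**Working it through.** **1. The plan's own figure.** The 93 per arm cannot be reproduced, because no endpoint, effect or standard deviation is given. It can only be back-solved under an assumption. For one two-sided 5% comparison of means with 80% power:

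d = (z₀.₉₇₅ + z₀.₈₀) × √(2/n) = (1.960 + 0.842) × √(2/93) = 0.411

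The t-test version gives 0.413. A one-sided test would give 0.365. Other routes also reach 93, for example a comparison of 30% with 50% without continuity correction. So d ≈ 0.41 is an assumption and not a figure from the article.

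**2. Size of the primary set.** Day 1 is drawn before dosing and cannot show a treatment effect, so it is left out.

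- Cell markers: 14 × 6 post-baseline draws = 84 tests. Counting dendritic cells once gives 13 × 6 = 78.
- Genes, if tested one by one: 84 × 3 post-baseline draws = 252 tests.
- Together: 84 + 252 = 336.

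This does not count antigen density separately. It follows the four array days in Outcome Measures, although Table 1 ticks the sample for these responses at all seven draws.

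**3. Type I error without adjustment, no true effect anywhere.**

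- Expected false positives, whatever the correlation: 84 × 0.05 = 4.2 for the markers; 336 × 0.05 = 16.8 if the genes are also tested singly.
- Familywise error for the 84 marker tests if independent: 1 − 0.95⁸⁴ = 98.7%.
- Related markers measured repeatedly are correlated. Simulation with assumed exchangeable correlations gives:

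| Between markers | Over time | Familywise error, 84 tests |
|---|---|---|
| 0 | 0.5 | 96% |
| 0.3 | 0.7 | 87% |
| 0.7 | 0.9 | 46% |

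- For all 336 tests with one common pairwise correlation: about 96% at 0.5, 47% at 0.8 and 28% at 0.9.

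**4. Power once the family is protected.** Take the assumed d = 0.413, 93 per arm and a Bonferroni level of 0.05/k. The noncentrality is 0.413 × √(93/2) = 2.82. Power for a single given marker, and the difference detectable with 80% power (t-test), are:

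| Tests k | Level 0.05/k | Power at d = 0.413, 93 per arm | Detectable d, 93 per arm | Detectable d, 90 per arm |
|---|---|---|---|---|
| 1 | 0.0500 | 80% | 0.41 | 0.42 |
| 3 | 0.0167 | 66% | 0.48 | 0.49 |
| 14 | 0.0036 | 45% | 0.56 | 0.57 |

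The last column is there because 112 per arm less 20% is 112 × 0.8 = 89.6, about 90 and not 93.

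**The case against.** **The sample size need not describe one test.** The section speaks of parameters in the plural. It does not say whether 93 is the largest of several calculations, or whether 5% is per test or familywise. This stands: the fall from 80% to 45% holds only if 93 was sized for one unadjusted comparison, so it is conditional.

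**A false positive is not certain.** A reader might infer that a positive result is nearly guaranteed under the null. That is fair for independent or moderately correlated markers, but under strong correlation the figure is 46% for the marker tests and 28% for all 336. Well above 5% is supported; near certainty is not.

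**Neither property need fail outright.** A reader might also infer that both the 5% and the 80% are false. An adjustment in an analysis plan that is not shown could restore 5%, and one unadjusted comparison could have 80% power at some unstated effect. What is missing is any showing that both hold for the declared primary set.

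**The power loss depends on what counts as success.** If all 14 markers truly shifted by 0.413, Holm would give about 55% to 57% power per marker. The chance that at least one passes would be about 97% at a correlation of 0.3, 82% at 0.7 and 68% at 0.9. The 45% describes the case where one marker moves. This also stands, but the article does not define success either way.

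**The gene count is inferred.** Outcome Measures makes the innate and acquired responses primary. It does not commit to 84 single-gene tests, and a pathway-level analysis is not excluded. The 252 and 336 are therefore conditional, while the 84 marker tests do not depend on them.

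**Conclusion.** The concern holds in this form: the article states 5% and 80% for an unnamed limited set, declares a much larger primary set with no lead endpoint, and does not show that the two properties hold together for it.

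Without adjustment, the familywise error for the post-baseline marker tests alone is about 46% to 99% over the correlations assumed. About 17 false positives are expected if the genes are also tested one by one. With Bonferroni protection, power for a single marker is about 66% with three markers and 45% with 14, provided that 93 was sized for one two-sided comparison of means at d ≈ 0.41. The correlations and that d are assumptions; the marker and visit counts come from the article.

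This is more than omitted detail, because the sections conflict on what is primary. It should be corrected before any result is seen.

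**What to change.** Before unblinding and before assay results are seen:

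1. Name a small set of primary parameters, each at one time point or as one average over the post-baseline draws. They must be chosen afresh, since the Sample Size section does not identify those behind the 93.
2. Control that family at 5%, for example with Holm. Other valid procedures would serve.
3. Move all other markers and visits, and the genes, to secondary or exploratory status with false discovery rate control.
4. Restate power as the detectable standardised difference for the chosen family at the evaluable number expected. As a Bonferroni bound at about 90 per arm, this is about 0.42 for one test, 0.49 for three and 0.57 for 14.

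**Cost.** No new data are needed: the article reports enrolment complete and the immunological assays still to be done, with unblinding at the end of the study. It is not just a note to file, however. The Protocol Amendments section restricts amendments to exceptional cases and requires written justification, Ethics Committee approval and notification to the registry. Fewer results can be called primary, and the stated detectable effect becomes larger.

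### The 20% attrition allowance was computed as 93 × 1.2 instead of 93 / 0.8, so 112 per arm covers 17% loss, not 20%

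*Protocol article*

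**What the plan says.** The Sample Size section of the protocol article gives a type 1 error of 5%, power of 80%, and the resulting requirement: "it was estimated that there would be 93 participants each in the intervention and control groups, with a total of 186 participants". It then adds an allowance for loss to follow-up: "If this loss to follow-up is considered at 20%, a total of 112 participants have to be enrolled in each group", for a total of 224. It does not state the formula used for the allowance.

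The Methods paragraph of the Abstract repeats the target in different words: "112 participants per arm (with an expected dropout of 20%) will be screened".

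The Study Design section fixes equal allocation ("using an allocation ratio of 1:1"), so the per-arm figures double directly to totals. No endpoint, effect size, standard deviation, test or sidedness accompanies the 93. The section itself says "Owing to the scarce availability of literature, it would be quite challenging to hypothesize the assumption".

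**The concern.** The section prints three numbers that must fit together: 93 needed, 20% lost, 112 enrolled. They do not. An attrition allowance should be set so that the required number remains after the expected loss, which means dividing by the retained fraction. Multiplying by one plus the loss rate applies the 20% to the wrong base and always gives too few.

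What is at stake is the reliability of the design statement. A reader of a null result would assume that the trial kept its 80% power with up to a fifth of participants lost. Attrition is a real possibility here. Follow-up runs for 66 days with seven blood draws. The sections on dropout, withdrawal and concomitant care also list several routes out of the study, including poor compliance, concomitant viral disease, prohibited therapy and missed visits.

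**Working it through.** **Inputs, all from the Sample Size section unless noted**

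- Required per arm before attrition: 93 (186 in total)
- Type 1 error 5%, power 80%
- Expected loss to follow-up: 20% (also in the Abstract)
- Enrolment target: 112 per arm (224 in total)
- Allocation 1:1 (Study Design)

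**Step 1: reproduce the plan's figure.** Required n × (1 + loss) = 93 × 1.20 = 111.6, rounded up to 112. This matches the plan exactly.

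**Step 2: the figure that fits the stated inputs.** Required n / (1 − loss) = 93 / 0.80 = 116.25, rounded up to 117 per arm, or 234 in total. The gap is 117 − 112 = 5 per arm, 10 in total. Check: 117 × 0.80 = 93.6, which is at least 93.

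**Step 3: what 112 leaves at the plan's own loss rate.** 112 × 0.80 = 89.6 per arm. The shortfall is 93 − 89.6 = 3.4, that is 3 to 4 participants per arm.

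**Step 4: the loss that 112 does cover.** 112 − 93 = 19 losses per arm, and 1 − 93/112 = 17.0%.

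**Step 5: effect on power.** The plan gives no effect size, so I assume that 93 per arm gives exactly 80% power and solve for the standardised difference d that this implies.

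Two-sided normal approximation: d = √(2/93) × (1.960 + 0.842) = 0.411. Power at n per arm is Φ(d × √(n/2) − 1.960). For n = 89.6 this is Φ(0.411 × √44.8 − 1.960) = Φ(0.790) = 78.5%.

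The result under other assumptions:

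| Assumption | Power at 89 | Power at 89.6 | Power at 90 |
|---|---|---|---|
| Two-sided normal, d = 0.411 | 78.3% | 78.5% | 78.7% |
| Two-sided t-test, d = 0.413 | 78.2% | 78.5% | 78.7% |
| One-sided normal, d = 0.365 | 78.5% | 78.7% | 78.8% |
| Two proportions, e.g. 30% vs 50% | 78.2% | 78.5% | not run |

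If 93 was itself rounded up from just above 92 (d = 0.413 in the normal formula), power is 78.9% at 89.6 and 79.1% at 90. Every case lies below 80%, by about 1 to 2 percentage points.

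**The case against.** The arithmetic is not in dispute. The case on the other side concerns weight and reading.

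- **The effect is small.** Power falls by about 1.5 points, and no endpoint, analysis or participant number changes. This stands, and it limits how much should be made of the point.
- **The power figures are conditional.** They rest on an effect size solved back from 93, and nothing in the article lets a reader check that 93 gives 80%. This also stands, so any restated power must carry that condition. The shortfall in numbers and the 17.0% tolerance need no such assumption.
- **Late dropouts still contribute data.** The Sample Size section speaks of participants, not of complete cases. The Statistical Analysis section names intention-to-treat as well as per-protocol analysis, at seven time points. Someone lost late still has earlier samples, so 89.6 is the worst case for the early time points. That is fair, but the allowance exists to cover loss, and it does not cover the loss rate stated for it.
- **The 20% might be meant as an uplift on 93.** The Abstract rules this out, because it attaches the expected dropout of 20% to the 112 per arm.
- **Achieved numbers are unknown.** The Results section reports enrolment complete without giving the number enrolled or lost. The actual shortfall therefore cannot be known from the article, but the planned figures remain inconsistent.

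**Conclusion.** The concern holds. The three printed figures cannot be reconciled: 112 comes from multiplying by 1.2, and the stated inputs call for 117 per arm. At the plan's own 20% loss about 90 per arm remain, 3 to 4 fewer than required, and 93 is preserved only up to 17.0% attrition. These statements follow from the document alone.

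The power consequence, about 78.5% instead of 80%, assumes that 93 per arm gives exactly 80% and that the lost participants contribute nothing to the comparison. It is a modest loss that would not by itself change the trial's conclusions. The correction is still worth making, because the sample-size statement is wrong as written and easily put right.

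The Abstract's description of the 112 per arm as the number screened is a clerical slip. Arms exist only after randomisation, which follows two screening stages, and the Sample Size section says enrolled. It adds no weight to the finding.

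**What to change.** Since enrolment is closed, correct the statement and leave the sample as it is. In the Sample Size section, replace the attrition sentence with wording such as: *With 112 participants enrolled per arm (224 in total), at least 93 per arm remain if attrition does not exceed 17%. At 20% attrition about 90 per arm would remain, with about 78.5% power, assuming that 93 per arm gives 80%.*

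In the Methods paragraph of the Abstract, change the verb so that the 112 per arm are enrolled, and align the dropout figure with the corrected sentence.

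The cost is one sentence, a small edit to the Abstract, and a slightly less favourable design statement. No additional participants and no change to the analysis are needed.
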